## Abstract

**Introduction:**

Currently, all people with diabetes (PWD) aged 12 years and over in the UK are invited for screening for diabetic retinopathy (DR) annually. Resources are not increasing despite a 5% increase in the numbers of PWD nationwide each year. We describe the rationale, design and methodology for a randomised controlled trial (RCT) evaluating the safety, acceptability and cost-effectiveness of personalised variable-interval risk-based screening for DR. This is the first randomised trial of personalised screening for DR and the largest ophthalmic RCT in the UK.

**Methods and analysis:**

PWD attending seven screening clinics in the Liverpool Diabetic Eye Screening Programme were recruited into a single site RCT with a 1:1 allocation to individualised risk-based variable-interval or annual screening intervals. A risk calculation engine developed for the trial estimates the probability that an individual will develop referable disease (screen positive DR) within the next 6, 12 or 24 months using demographic, retinopathy and systemic risk factor data from primary care and screening programme records. Dynamic, secure, real-time data connections have been developed. The primary outcome is attendance for follow-up screening. We will test for equivalence in attendance rates between the two arms. Secondary outcomes are rates and severity of DR, visual outcomes, cost-effectiveness and health-related quality of life. The required sample size was 4460 PWD. Recruitment is complete, and the trial is in follow-up.

**Ethics and dissemination:**

Ethical approval was obtained from National Research Ethics Service Committee North West – Preston, reference 14/NW/0034. Results will be presented at international meetings and published in peer-reviewed journals. This pragmatic RCT will inform screening policy in the UK and elsewhere.

**Trial registration number:**

ISRCTN87561257; Pre-results.

Strengths and limitations of this studyOur study addresses one of the primary current issues in the field of screening for diabetic retinopathy: the safety of extending the interval between episodes.Our study has significant novelty applying a personalised approach to a whole population intervention, using routinely collected data from primary and secondary care, a risk calculation engine that allows generalisation and evaluated in the first RCT conducted on screening for diabetic retinopathy.Strengths include the substantial involvement of people with diabetes in the design and implementation, large numbers of participants for tight confidence limits, pragmatic solutions for variable quality routine National Health Service data and the independent analysis by an accredited clinical trials unit.The risk calculation engine ​has been internally validated but will require further external validation before implementation could be considered elsewhere.The trial only recruits people currently attending screening and does not identify the impact for people who currently do not attend.

## Introduction

### Background

Diabetes mellitus (DM) is a life-long condition associated with the development of various macrovascular and microvascular complications, including diabetic retinopathy (DR) and maculopathy (a subgroup within DR). These are progressive conditions of the retina and macula, which can lead to visual impairment (VI) and blindness. There are an estimated 3.8 million people with diabetes (PWD) aged 16 years and over in England,^1^ of whom almost 1 million are undiagnosed. Nearly all people with type 1 diabetes^2^ and over 60% with type 2 diabetes^3^ will develop some degree of DR after 20 years of having diabetes.

DR affects people of all ages and is the most common cause of blindness in people of working age in most developed countries worldwide. In the UK, this position has changed. Liew *et al*
4 reviewed the causes of blindness certifications in working age adults in England and Wales in 2009–2010 and reported that DR had dropped to the second most common cause compared with 10 years earlier. Tighter control of glycaemia and hypertension will have contributed to this, but it is probable that screening for DR has also played a key role.

The early stages of DR (background and mild pre-proliferative) are asymptomatic and do not require any treatment. Sight-threatening diabetic retinopathy (STDR; an umbrella term that encompasses sight-threatening levels of retinopathy and maculopathy) requires close monitoring by an ophthalmologist, and sometimes treatment, to prevent VI.

Treatment (by laser photocoagulation or intravitreal injections) aims to stop progression and stabilise retinopathy. Treatment cannot always reverse the process once vision is lost. Screening is therefore recommended to identify STDR at the optimal time-point for treatment. Previous studies have shown that screening for DR is a highly cost-effective intervention^5 6^: the higher the take-up rates for screening, the higher the cost-effectiveness.^7^

Annual systematic screening for DR for all PWD aged 12 years or older was introduced across the UK by 2007. A 1-year interval between screening invitations (screen interval) was based on expert opinion, rather than direct evidence. In 2016, the UK National Screening Committee recommended that PWD at low risk of sight loss could be screened every 2 years, but this has not yet been adopted. This stratified approach was based on evidence from a large observational study in one English programme and a cost-effectiveness analysis.^8^ The findings were validated in the Welsh, Scottish and Northern Ireland programmes and four more English programmes. Stratified screening is due to be implemented in Scotland.

Available evidence shows that many people at low risk of developing referable DR between annual screening appointments could safely be screened less often,^9^ while others are at high risk and might benefit from more frequent screening.^10^ In 1996, Davies *et al*
11 used simulation modelling of published data and concluded that biennial screening could be considered where patient compliance and screening sensitivities were both high. Data on 10-year incidence from the Liverpool Diabetic Eye Study—for a population of people with type 2 DM and enrolled in a systematic screening programme—suggested that a 3-yearly screening interval could be adopted for PWD with no retinopathy at baseline, but yearly or more frequent screening was recommended for people with higher grades of retinopathy or insulin use.^12^ Similar results were shown for type 1 DM.^13^ In Sweden, biennial screen intervals have been used for some time for subjects without retinopathy.^14^ A study carried out in Malmo prospectively followed people with type 2 DM and no retinopathy and concluded that it appeared safe to adopt 3-year intervals^15^ as suggested by the Liverpool group. However, this group of PWD were compliant (only 9% did not attend for follow-up) and had a short duration of diabetes (6±6 years) and good control (glycated haemoglobin (HbA1c) 6.4%±1.5% at baseline and 6.3%±1.3% at 3-year follow-up).

Two studies have looked at stratified screening and shown that the risk of progression to STDR is significantly higher for those with background DR (BDR) in both eyes than those with BDR in only one or in neither eye.^16 17^ The first of these two studies suggested that combining the results from two consecutive years of photographic screening enabled estimation of the risk of future development of STDR. People with no DR on two consecutive visits were deemed to be low risk.

So why hasn’t an extended interval in screening for STDR been more widely adopted? There has been considerable concern about the safety of extending screen intervals and, to date, no randomised controlled trial (RCT) has reported.^9^ The experience of Sweden and Scotland is reassuring, but the populations are much smaller and generally better engaged. If people receive the impression that they are at low risk, they may disengage with other aspects of diabetes care. Despite encouraging findings from our group in 2003, in the absence of the required safety data, it appears unwise to recommend 2-year or 3-year intervals for PWD at low risk without further evidence.

### Rationale for an RCT

With this in mind, we designed an RCT to investigate the safety of extending screening intervals in low-risk PWD. We included the emerging theories and technologies of risk prediction and personalisation to develop a risk-based variable-interval screening approach and incorporated an economic evaluation.

In addition to severity of retinopathy, the risk of development and progression of DR to a level that requires treatment is related to age, gender,^1 2^ duration of diabetes, glycated haemoglobin (HbA1c) levels,^18–23^ blood pressure,^24–26^ lipid levels^27^ and proteinuria.^28^ If the contribution of each risk factor to overall risk (as well as the overall contribution in combination) could be calculated, and data on each risk factor were available for individuals, individual risks could be estimated and screening frequencies could be tailored to the level of personal risk.^29^

We developed a risk calculation engine (RCE) using a longitudinal dataset from our local diabetic population to predict the risk of developing STDR and have reported confident estimates of the risk of having STDR.^30^ In Iceland, a similar risk algorithm has also been developed to estimate the risk of development of STDR but based on modelling of historic epidemiological data on a limited number of risk factors for DR.^31^ In the Netherlands, a screening model based on patients’ risk has been validated in 3319 people with type 2 diabetes as part of the Hoorn Study.^32^ We embedded a patient and public involvement (PPI) group in the development of the RCE and subsequent design of the trial. There has been scant research into people’s understanding of screening and their views about introducing variable screening intervals. Yeo *et al*
33 reported that extended intervals may be acceptable to the majority of PWD if there was adequate evidence to support such a change.^33^ We found that over a series of workshops the PPI volunteers became expert in the field and made important design decisions.

We believe that screening for referable DR at intervals based on individual risk could be both safe and cost-effective compared with annual screening. In this paper, we report the key features of the design of an RCT designed to test this hypothesis.

### Trial status

The trial opened to recruitment on the 12 November 2014. The first patient was randomised on the 19 November 2014. The trial was closed to enrolment on the 31 May 2016. The target of 4460 patients was reached. The programme grant completes on 30 April 2019.

### Patient and public involvement

We have included members of our PPI Group in all stages of the design of the trial. Our PPI group consists of seven individuals and has met at regular intervals throughout the lifetime of the trial. Individuals are active participants in the programme and trial steering committees, programme investigators committee and trial management committee. Individuals were involved in the concept and development of the research questions, design of the trial and the grant application. One patient is a coinvestigator and was closely involved in designing the intervention including reviewing the potential burden. The group was involved in the choice of risk factors for consideration for the RCE and secondary outcome measures. They developed a set of patient-centred outcomes, most notably adding VI and need for treatment, which they viewed as particularly important to patients. They considered the chance of missing disease if screen intervals were extended and after several structured sessions settled on a 2.5% risk as an acceptable limit. They were not involved in actual recruitment to the trial, but they visited the screening centres and observed recruitment and gave constructive comments, which improved the process.

Regarding dissemination of results, these will be sent to the participants’ general practitioners. Participants have also been advised to let the researcher know if they would like a summary of the results themselves.

### Participants, interventions and outcomes

#### Trial design

The ISDR RCT had 1:1 allocation to an indivdualised risk-based screening recall (6, 12 or 24 months) or annual screening (current routine care).

#### Objectives

The objective of the ISDR RCT is to evaluate the safety, acceptability and cost-effectiveness of personalised screening in a whole population setting. The main aim is to assess the relative safety of variable-interval screening as measured by attendance rate. We will test the hypothesis that the difference in attendance rates between the two pathways is within an acceptable equivalence margin.

#### Study setting

This single site trial is being conducted in all seven screening clinics in the LDESP, which is part of the English National Diabetic Eye Screening Programme (NDESP).

#### Study population

PWD registered with a GP whose postcode is in the city boundaries of Liverpool and attending for screening for DR were invited to enter the trial. The inclusion and exclusion criteria are given in table 1.

**Table 1 T1:** Inclusion and exclusion criteria in the personalised variable-interval risk-based screening for diabetic retinopathy randomised controlled trial

Inclusion criteria	Exclusion criteria
Adults, young people and children who are aged ≥12 years.	Under age 12 years.
Due to be offered an appointment for retinal screening during the recruitment period.	
Registered with a participating GP practice.	Are not registered with a participating GP practice.
Are included in the study data warehouse (have not opted out).	Have opted out from the study data warehouse.
Have no retinopathy or have retinopathy and maculopathy less than the definition of screen positive diabetic retinopathy.	Have screen positive diabetic eye disease or significant other eye disease requiring referral to the HES.
Have gradeable digital retinal images in both eyes.	Are ineligible for screening for whatever reason, including having ungradable digital retinal images, which includes patients who have only one eye or an ungradable eye with no visual potential.
Give their informed consent for participation.	Do not give consent for participation in the RCT.
Are not involved in any trial investigating a treatment aiming at preventing or modifying the development of STDR.	Are involved in any trial investigating a treatment aiming at preventing or modifying the development of STDR.

GP, general practitioner; HES, hospital eye service; STDR, sight-threatening diabetic retinopathy.

The schematic of the ISDR RCT study design is given in figure 1.

**Figure 1 F1:**
[figure not shown]
Schematic of the ISDR RCT trial design.

### Data flows

Data flows are shown in figure 2. Data on the participant’s retinopathy status feeds automatically from the screening software (OptoMize, EMIS health) into the data warehouse (DW) and then to the randomisation and RCE programmes on a daily basis. The ISDR DW automatically populates the majority of the fields in the baseline and follow-up electronic CRFs (OpenClinica), including data that allowed randomisation to occur.

**Figure 2 F2:**
[figure not shown]
Data flows. In step 1, data for consented participants are requested from OptoMize, passed to the DW and cleaned prior to storage. In step 2, data are exchanged between the DW and OptoMize (subjects whose risk needs to be calculated are sent to the DW, subjects for whom their risk and therefore recall interval has been calculated is returned to OptoMize for appointment letter generation). In step 3, the participants’ risk is calculated (when all the covariates are available); if randomisation is required, they are then randomised. The data are then stored in the study database and the DW. All processes in steps 1 and 2 involve identifiable data; the processes in step 3 all use pseudanonomised data for security reasons (the trial team with access to the trial database do not have a need to see raw identifiers). Step 1 occurs on a bimonthly period, steps 2 and 3 occur on a daily basis. Under ideal conditions, it takes 3 days for the data to pass through all parts of steps 1 and 2; this is due to an air gap (manual transfer) at step 2 between the DW and the National Health Service systems. CRF, case report form; DW, data warehouse.

### Primary endpoint

The primary outcome is the attendance rate for follow-up screening in the two arms of the study. Non-attendance is defined as failure to attend any screening appointments within 90 days of the expected follow-up date, irrespective of how many appointments they had been sent.

### Secondary endpoints

Number of cases of STDR detected.Retinopathy level at screening.Maculopathy level at screening.Number of false positive screening episodes.Number of screening appointments.Number of diabetes assessment clinic appointments.Number of other eye appointments for DR.Visual acuity (log of the minimum angle of resolution [logMAR]).New VI (≥+0.30 and ≥+0.50 logMAR),New VI (≥+0.30 and ≥+0.50 logMAR) which, in the opinion of an experienced clinician, is due to DR.Number of missed appointments to screening.Patient acceptability measures (using a questionnaire designed for the RCT).Quality-adjusted life years (QALYs) estimated using EQ-5D-5L and Health Utilities Index Mark 3 (HUI3).Cost per QALY.

### Intervention, assessments and procedures

The ISDR DW is a relational database that stores both the data and how the data are related. The Liverpool GPs gave permission for their PWD to be directly contacted to give permission for the data held in primary care relating to their diabetes to be transferred to the DW. The DW was established to collate and dynamically link individual risk factor data from GP practices, STDR outcome data from the DR assessment clinic at St Pauls Eye Unit and the LDESP screening software (OptoMize). This central data repository was used to develop the locally applicable RCE described above using a continuous Markov model.

The RCE was developed using routinely collected primary and secondary care data from 11 806 PWD (46 525 screening episodes) in the LDESP. A detailed description of the RCE has already been published.^30^ In brief, the final covariates for the RCE were selected using a three-step decision process. A number of risk factors for developing STDR were identified in the published literature and in preliminary work in Liverpool. These potential covariates were reviewed by the clinical team and the PPI group, and potential additional covariates were suggested. Potential covariates with a missingness rate of less than 20% in the DW were identified. Then a statistical evaluation of the predictive value of each remaining covariate was undertaken. The covariates selected were disease state (current retinopathy levels in both eyes); age; duration of diabetes; glycated haemoglobin; systolic blood pressure; and total cholesterol. The results suggested that implementing personalised risk-based intervals would reduce the number of screen episodes by 30%.

Our PPI group defined the degree of risk (up to 2.5% risk of developing screen positive DR) acceptable to PWD, allowing assignment of individuals to screen intervals at the time points 6, 12 or 24 months. The choice of these intervals was based on a review of the available literature, our data and consensus between the PPI and research teams. Following each negative screening outcome, individuals are assigned to the longest recall period up to 24 months at which their risk estimation would not exceed the 2.5% threshold.

### Consent

Individuals received a patient information leaflet with all the details of the trial with their screening appointment reminder letter. On attending the screening clinic, they were approached by trained researchers to establish whether they wished to participate in the trial. If they expressed an interest, the researcher took written informed consent and enrolled them into the trial. If an individual subsequently requested to be withdrawn from the trial, they reverted to routine care. Reasons for, and level of, withdrawal were collected.

### Randomisation

Randomisation could only be completed once the individual’s retinal images had been graded, as it was only possible at this point to complete the inclusion and exclusion criteria. PWD who screened positive due to DR, other eye disease or ungradable images were therefore consented but were not included in the trial.

Eligible PWD were randomly allocated to the personalised risk-based screening recall or the usual fixed annual interval. Participants were stratified by clinic and age (<16 and ≥16 years old). The screening clinics in Liverpool had different proportions of PWD in hard to reach groups, such as minority ethnic groups, attendance rates and social deprivation indices.

After randomisation the RCE was used to generate the individual’s recall period in the personalised arm of the trial and the data was sent back to the screening software.

### Study visits and assessments

At each follow-up visit, PWD randomised to the personalised risk-based screening arm have their risk recalculated and the next recall interval determined accordingly.

### Health economics

Table 2 shows the trial intervention diagram.

**Table 2 T2:** Trial intervention diagram

Procedures	Screening	Baseline	Randomisation	Follow-up schedule						Study completion	Premature discontinuation
				6 months*	12 months*	18 months*	24 months*	30 months*	36 months*		
Signed consent form	*X*										
Visual acuity (logMar)		*X*		*X*	*X*	*X*	*X*	*X*	*X*		
Visit questionnaire		*X*									
QoL questionaire† (HUI3 and EQ5D)		*X*		*X*	*X*	*X*	*X*	*X*	*X*		
Assessment of eligibility criteria	*X*	*X*	*X*								
Randomisation			*X*								
Digital imaging		*X*		*X*	*X*	*X*	*X*	*X*	*X*		
Acceptability questionnaire									*X*		

*PWD are randomised to two arms. In one arm, individuals attend at 12-month intervals. In the other arm, individuals attend at 6, 12 or 24 monthly intervals.

†The EQ-5D-5L and HUI3 data will be collected on around 700 eligible PWD and repeated at each visit for those individual PWD. Data will be stratified to balance equal numbers of PWD in each arm and representation from all screening sites.

HUI3, Health Utilities Index Mark 3; QoL, quality of life; PWD, people with diabetes.

A health economics questionnaire, incorporating the health-related quality of life (QoL) questionnaires EQ-5D-5L (an instrument to meaure health state developed by the EuroQol group)^35^ and Health Utility Index 3 (HUI3)^36^ and a bespoke visit questionnaire,^37^ was completed by the first 868 eligible PWD enrolled into the study (a minimum of 700 PWD was required to provide sufficient data). The QoL questionnaires are repeated at every subsequent follow-up visit for those PWD who completed it at baseline.

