### Sample size and planned analyses

The primary aim is to assess the relative safety of personalised risk-based interval screening as measured by equivalence in attendance rates. The analysis will test the hypothesis that the difference in attendance rates at the first follow-up between the two pathways is within the acceptable range δ=0.05. If the bounds of the 90% CI for the difference in attendance rate are found to be within the confidence limits (−δ,δ (ie, (−0.05 to 0.05)), the results would support equivalence.

The estimated minimum number of patients required is 3940. With an expected loss to follow-up rate of 6% per year due to death and other exclusion from screening (note that non-attendance is the primary outcome and therefore is not factored here), the target for recruitment (randomised into the trial) was 4460 patients (4460*0.94*0.94=3940).

A secondary aim is to investigate whether personalised screening can be considered as non-inferior in detection of STDR when compared with annual screening. The STDR detection rate predicted for the usual care pathway during the 2-year follow-up is approximately 6%, based on data from the LDESP. The sample size required to address the first question (n=4460 patients randomised with 3940 patients retained after 2 years from baseline) will permit us to test for non-inferiority in STDR detection with a maximum allowable reduction of 1.5% of the personalised care pathway compared with standard care, with 5% significance level and power between 60% and 65%.

We will undertake subgroup analyses to assess differences in attendance rates between the two arms for the three different retinopathy groups (the risk groups will be defined based on the individual baseline estimated risk of developing STDR). A logistic mixed-effects model that takes into account the patient’s covariate information over time (including retinopathy level, HbA1c, systolic blood pressure, total cholesterol, disease duration, and age), and screening clinic (clustered data) will be fitted with attendance (yes/no) at the first screening visit as the outcome variable. The random effects of the model will account for the variability by screening clinic.

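### The acceptability questionnaire is scheduled only at 36 months, so earlier withdrawers are absent from the acceptability result, which may be overstated in the personalised arm

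*Protocol article*

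**What the plan says.** The Objectives section states that the trial is to "evaluate the safety, acceptability and cost-effectiveness of personalised screening in a whole population setting". Under Secondary endpoints, the matching entry is "Patient acceptability measures (using a questionnaire designed for the RCT"; no other instrument for acceptability is named.

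Table 2 (Health economics section) sets out the assessments. The row "Acceptability questionnaire" has one mark, under 36 months. The table also has columns for study completion and premature discontinuation; both are blank in this row and in every other row.

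On withdrawal, the Consent section says: "If an individual subsequently requested to be withdrawn from the trial, they reverted to routine care". It adds: "Reasons for, and level of, withdrawal were collected". Trial design identifies routine care with the annual arm: "1:1 allocation to an indivdualised risk-based screening recall (6, 12 or 24 months) or annual screening (current routine care".

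Sample size and planned analyses ends with a general commitment to sensitivity analyses under different missing-data mechanisms. It does not mention acceptability.

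**The concern.** Leaving the trial because of the assigned interval is a direct sign that the interval was not acceptable. If the questionnaire is answered only by those still in the trial at 36 months, that sign is lost from the endpoint.

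The loss may not be even between arms. According to the Consent and Randomisation sections, people consent at the clinic and are randomised later, once their images are graded; a personalised recall interval is generated after that. They agree to take part before knowing their interval. Someone who then objects to a 6- or 24-month recall can return to annual screening by withdrawing. Someone in the annual arm gains no change of interval by doing so.

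At stake is how far the result for a stated objective can be trusted. Whether people accept variable intervals bears on the screening policy that the trial is meant to inform.

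**Working it through.** **1. Who can answer.** The only scheduled administration is at 36 months. A participant who withdraws before then has no scheduled opportunity to answer.

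**2. Whose interval changes on withdrawal.** Routine care is annual screening, so:
- annual arm: 12 months before, 12 months after, no change;
- personalised arm, currently on 12 months: no change;
- personalised arm, currently on 6 or 24 months: changes to 12 months.

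The incentive is therefore confined to part of one arm. The article does not say how large that part is, and risk is recalculated at each follow-up visit, so membership can shift.

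**3. The article's own attrition figure.** It assumes an "expected loss to follow-up rate of 6% per year due to death and other exclusion from screening". The stated figures reproduce: 4460 × 0.94 × 0.94 = 3940.9, against the stated 3940; and 3940 / 0.94² = 4459.03, against the target of 4460. If the same rate continued to 36 months, 4460 × 0.94³ = 3704 would remain (83.1%). This loss is attributed to death and exclusion from screening. It is not split by arm and says nothing about withdrawal over the interval, so it cannot be used to size the bias.

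**4. Size under assumed values.** Let w be the share of an arm that leaves over the interval, A the proportion of respondents who find it acceptable, and L the proportion of those leavers who would have said so. The rate in the whole arm is (1 − w)A + wL, so the respondents-only rate is too high by

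A − [(1 − w)A + wL] = w(A − L).

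The article gives none of these three values. Assume A = 0.80 to 0.90 and L = 0 to 0.5, so that A − L runs from 0.30 to 0.90:

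| w (assumed) | Overstatement in that arm, points |
|---|---|
| 0.5% | 0.15 to 0.45 |
| 2% | 0.6 to 1.8 |
| 6% | 1.8 to 5.4 |

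With the same A and L in both arms, the bias in the difference (personalised minus annual) is (w for personalised − w for annual) × (A − L):

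| w personalised / annual (assumed) | Bias in the difference, points |
|---|---|
| equal | 0 |
| 3% / 1% | +0.6 to +1.8 |
| 1% / 3% | −0.6 to −1.8 |

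**5. What the sensitivity analysis would show.** Counting interval-related leavers as not acceptable sets L = 0, so the rate becomes A(1 − w). For A = 0.90 and w = 2%, it is 0.90 × 0.98 = 88.2%, against 90% without them.

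**The case against.** Four objections carry weight.

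- **The blank cell is weak evidence.** The premature discontinuation column is empty in every row, yet the Consent section says that reasons for and level of withdrawal were recorded. The column is evidently not a full list of what happens at that point. A reader might infer from it a rule that withdrawers are never asked; the article states no such rule. The point rests instead on the single scheduled administration at 36 months.
- **The handling of withdrawers in the analysis may be specified elsewhere.** A condensed article can leave that to the full protocol or the analysis plan, and its absence here is not an error. The schedule is different: the article does fix it, and a questionnaire answer never collected cannot be supplied later by an analysis plan.
- **Missing-data scenarios are already planned.** This is so, and informative dropout is the kind of problem they address. They are general, however, and varying an assumption tells less than using a recorded reason that names the interval.
- **The direction and size are not established.** A reader might infer that withdrawers come mainly from the personalised arm and that acceptability is overstated there. The documents show an incentive, not a rate. A figure as high as 9.0 points can be produced (0.90 × 0.10), but it needs 10% of the arm to leave over the interval and every one of them to find it unacceptable. Carrying all of it into the difference between arms also needs no such leavers in the annual arm. Nothing in the article supports these values.

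Finally, the endpoint is described only as acceptability measures. The scale is not given, so treating it as a single proportion is itself an assumption.

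**Conclusion.** The point holds in a limited form. On the published schedule, withdrawal before 36 months removes a person from the acceptability endpoint. Only personalised-arm participants on 6- or 24-month recall can change their interval by withdrawing, so acceptability in that arm may be overstated. The direction assumes that people who leave over their interval find it less acceptable than those who stay.

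The size cannot be determined from the article. The illustrative 0.15 to 5.4 points depend entirely on the assumed w, A and L. The bias between arms vanishes if interval-related withdrawal is equal in both and would reverse if it were more common in the annual arm. If few people left for this reason, the effect is small, and reporting the count by arm would show that.

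This bears on one secondary endpoint, and the reasons already collected allow much of the repair. It is separate from whether 36 months is a suitable time: moving the date would still leave out those who withdrew before it.

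**What to change.** 1. Using the withdrawal reasons already collected, report the number of interval-related withdrawals by arm beside the questionnaire result.
2. Add a sensitivity analysis that counts these withdrawals as not acceptable, in both arms, for any acceptability item that can be expressed as acceptable or not. Show the result with and without them.
3. For withdrawals still to come, offer the acceptability questionnaire at discontinuation where the level of withdrawal allows contact, and mark it in the premature discontinuation column of Table 2.

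Items 1 and 2 cost only the coding of reasons already held, best done without knowledge of the questionnaire results. Item 3 costs one short form per withdrawal. The limits should be stated with the result: recorded reasons may be incomplete, some withdrawers will decline the form, and those who have already left can be covered only through their recorded reasons.
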